### **Comparing the SLE population: Analysis methods comparing PD exposed with PD-unexposed**

Mock-up Table 2. We will compare baseline characteristics across SLE strata, including Systemic Lupus Erythematosus activity and damage scores, patient-reported outcome measures, and pulmonary function tests, for all patients and by the presence or absence of thoracic disease. All 95% confidence intervals (95%CI) will be two sided. The analyses of the secondary outcomes will be performed in sequence. The 95%CI will not be adjusted for multiplicity and should not be used in place of hypothesis testing.

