## **Logistical regression: Searching for risk factors that are associated with presence of different forms of PD**

Mock-up Table 4. We aim to explore whether one or more clinical measures collected at baseline are associated with the presence of PD. The dependent variable will be the presence or absence of a PD condition of interest (i.e.,  $Y=1$  if yes, otherwise  $Y=0$ ). Logistic regression is the best approach for identifying predictors when the outcome variable is binary (i.e., presence vs. absence of PD) and the goal is to estimate the association between predictor variables and the probability of the outcome while enabling adjustments for potential confounders. Independent variables, as listed in Table 4 and appendix 3, will be analysed in univariate logistic regression to identify potential associations with clinically significant PD conditions. Odds ratios (ORs) with 95% CIs will be used to quantify the strength of associations, with 95% CIs excluding 1 considered indicative of potential significance. In multiple logistic regression analyses we plan to investigate associations that were significant by univariate analyses, however, only a subset of independent variables will be expected to remain statistically significant and independently associated with PD conditions.

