We plan to present results of PFT test of subtypes of PD (Airway disease, Pleural Disease, ILD, and SLS) and the contrast between groups with means, SD, and a 95% confidence interval for continues data or number and percentages for categorical data in appendixes, see Appendix 1 a-d.

We plan to present the prevalence of High-Resolution CT findings among the investigated study population is presented in an appendix, see appendix 2.

We plan to present results of the univariate logistic analyses, with Odds Ratio and corresponding 95%CI, of the association between selected baseline characteristics and the presence of PD, airway disease, pleural disease, ILD, and SLS in a table, see table 4.

**Table 4.** Impact of selected baseline characteristics and patient related outcome measures in groups of thoracic diseases investigated by univariate logistic regression analyses.

| PD Outcome
vs.
Baseline characteristics | PD
Odds
Ratio
(95%CI) | Airway
Odds
Ratio
(95%CI) | Pleural
Odds
Ratio
(95%CI) | ILD
Odds
Ratio
(95%CI) | SLS
Odds
Ratio
(95%CI) |
|--------------------------------------------------------|------------------------------------------|----------------------------------------------|-----------------------------------------------|-------------------------------------------|-------------------------------------------|
| Age, years                                             |                                          |                                              |                                               |                                           |                                           |
| Female sex, no (%)                                     |                                          |                                              |                                               |                                           |                                           |
| Disease duration, years                                |                                          |                                              |                                               |                                           |                                           |

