| dsDNA positive ever, no. (%)                           |                                          |                                              |                                               |                                           |                                           |
| SLEDAI 2K, score 0-105                                 |                                          |                                              |                                               |                                           |                                           |
| SLEDAI 2K, without PD, score 0-103                     |                                          |                                              |                                               |                                           |                                           |
| SLICC DI, score 0- 48                                  |                                          |                                              |                                               |                                           |                                           |
| SLICC DI, without PD, score 0-43                       |                                          |                                              |                                               |                                           |                                           |
| Dry cough, composite                                   |                                          |                                              |                                               |                                           |                                           |
| Dry cough, status:                              |                                          |                                              |                                               |                                           |                                           |
| Never, no. (%)                                         |                                          |                                              |                                               |                                           |                                           |

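### Univariate significance decides which variables enter the multiple logistic models, so adjustment for age, sex, smoking or disease duration is left to a test

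*SAP*

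**What the plan says.** The section on logistic regression gives a two-step rule.

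- **Screen.** "Independent variables, as listed in Table 4 and appendix 3, will be analysed in univariate logistic regression". The gate is the odds ratio's interval, "with 95% CIs excluding 1 considered indicative of potential significance". The section on comparing groups by PD states that "All 95% confidence intervals (95%CI) will be two sided", so the gate is a two-sided 5% test.
- **Multiple model.** "In multiple logistic regression analyses we plan to investigate associations that were significant by univariate analyses", with the expectation that "only a subset of independent variables will be expected to remain statistically significant and independently associated with PD conditions".

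The screen is run for five outcomes: "the presence of PD, airway disease, pleural disease, ILD, and SLS in a table, see table 4".

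Adjustment for confounders appears only as a general merit of logistic regression. No variable is named as forced in. There is no limit on model size, no shrinkage and no validation. On multiplicity, the group-comparison section says: "The 95%CI will not be adjusted for multiplicity and should not be used in place of hypothesis testing". The section Deviations from SAP mentions post hoc fitted analyses without describing them, so it cannot be read as replacing this rule.

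**The concern.** A univariate test is a poor guide to whether a variable confounds. A confounder whose effect is masked by a correlated exposure can show no univariate association and still bias the exposure's odds ratio when omitted. Under the stated rule such a variable leaves the model.

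Selection and estimation also use the same data, so a variable that passed the screen by chance tends to look significant again in the second model. The label of independence then claims more than the procedure delivers.

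The candidate pool adds to the difficulty. It lists the total activity score beside "SLEDAI 2K, without PD, score 0-103", the damage index in the same two forms, smoking, overlap, cough and chest tightness as composites and as status or component rows, and most lung-function measures both as a value and as a dichotomy. It also holds symptoms, lung function and current treatment, which may follow from PD. No rule keeps related versions out of the same model.

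At stake are the adjusted results for the secondary objective on associations with PD and its subtypes.

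**Working it through.** The SAP gives no sample size, event count or error rate for these models, so there is no figure of its own to reproduce. Sample size, prevalence, effects and correlations below are assumptions.

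**1. Size of the screen.** Table 4 holds 24 variables, counting each status variable once and treating the second overlap row as a header. Appendix 3 adds 40, not counting its repeats of SLEDAI 2K and SLICC DI. That makes 24 + 40 = 64 candidates per outcome.
- Expected false passes per outcome if all are null: 64 × 0.05 = 3.2. This does not need independence.
- Chance of at least one, if independent: 1 − 0.95^64 = 96.2%.
- All outcomes, less the four cells blocked in Table 4: 5 × 64 − 4 = 316 tests, and 316 × 0.05 = 15.8 expected.

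**2. Masked confounder.** One exposure (log-OR 0.5) and one confounder (log-OR −0.3), correlation 0.5, n=200, prevalence about 50%, 3,000 data sets. The rule adjusts only if the confounder's univariate |z| exceeds 1.96.

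| | Two-step rule | Always adjusted |
|---|---|---|
| Mean log-OR, all data sets (truth 0.5) | 0.37 | 0.51 |
| Coverage of 95% CI | 84% | 95% |

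The confounder was left out in about 97% of the data sets in which the exposure passed.

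**3. Confounder in the same direction.** At n=200 with log-ORs 0.5 and 0.3 and correlation 0.5, it was left out in about 6% of data sets where the exposure passed, and the rule's mean (0.51) and coverage (95%) matched full adjustment. Over the same-direction settings tried, n 150 to 300 and including a null exposure, the loss was about 1 to 20%. When a null exposure was selected and its confounder dropped, the mean OR was about 1.25 to 1.43 instead of 1.0.

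**4. Does the second step filter chance findings?** 60 noise candidates, correlation 0.3 within blocks, n=200, 400 runs at each prevalence. The comparison uses four fixed adjusters and tests the other 56 singly.

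| | Prevalence 50% | Prevalence 15% |
|---|---|---|
| Pass the screen | 3.0 | 3.0 |
| Still significant in the multiple model | 1.7 (56%) | 1.7 (59%) |
| Runs with at least one | 88% | 88% |
| Fixed adjusters: false findings | 2.8 | 3.0 |
| Fixed adjusters: runs with at least one | 94% | 93% |

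With 64 candidates, n 150 to 300, prevalence 15 to 60% and correlation 0 or 0.3, 51 to 81% of false passes stayed significant (1.6 to 2.6 per outcome), and 85 to 96% of runs had at least one.

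Per candidate the two-step rule gives 1.7/60 = 2.8% false findings, and single testing with fixed adjusters gives 2.8/56 = 5.0%. Step 4 therefore shows multiplicity. The case for a fixed adjustment set rests on steps 2 and 3.

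**The case against.** The analysis is declared exploratory, speaks of potential significance, and serves a secondary objective. Table 4 and Appendix 3 are labelled as univariate, and the SAP has no table shell for a multiple model. All of that stands and limits the severity. The exploratory label does not rescue the claim of independent association.

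Several stronger readings are tempting, but the material does not support them.

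- *Real confounders will be dropped.* This is a risk whose size depends on the direction of effects. It is large under masking and small for a strong confounder acting in the same direction.
- *About 60% stay significant where 5% should.* The 60% is conditional on having passed the screen, so 5% is not its benchmark.
- *A fixed adjustment set removes false positives.* It does not; in step 4 its count is higher.
- *Adjusted odds ratios are generally too far from the null and their intervals too narrow.* In the masking case the rule's estimate lies too close to the null. Among data sets where the exposure passed, the rule averaged 0.44 and the full model 0.60 around a truth of 0.5, so that comparison is distorted by selection and is no evidence for either method.
- *Near-duplicates will enter together.* The SAP does not say that all significant variables go into one model. It also blocks pleuritis and effusion as predictors of PD and pleural disease, and offers scores without PD. What can be said is that no rule prevents joint entry.

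The sentence can also be read as choosing only which exposures receive an adjusted analysis. The adjustment set is then unspecified, and selection by significance remains.

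**Conclusion.** The point holds at moderate severity. The SAP lets a 5% univariate test decide the content of its adjusted models and then attaches a label of independence that the procedure cannot support. With opposing effects the assumed example shows a shift in mean log-OR from 0.51 to 0.37 and a loss of coverage from 95% to 84%. With same-direction confounding the damage is small. About 1.7 chance findings per outcome survive both steps, a multiplicity problem of its own.

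These sizes rest on assumed sample size, prevalence, effects and correlations. The 3.2 expected false passes rest only on the candidate count and the 5% gate.

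A reader might infer that the study's main result is undermined. It is not: the primary objective is a prevalence, and neither that estimate nor the univariate odds ratios pass through this step.

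**What to change.** Replace the sentence on multiple regression with a rule along these lines:

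- Enter age, sex, smoking status and disease duration, all already in Table 4, in every adjusted model whatever their univariate results. Where events are few, reduce the set or fit with a penalised (Firth) likelihood.
- Report every other candidate one at a time with that adjustment. Never put a composite with its components, or a score with its version without PD, in the same model. Do not use symptoms, lung function or current treatment as adjusters.
- Describe the results as associated after adjustment for the pre-specified covariates, exploratory and not adjusted for multiplicity, and state how many candidates were tested.

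The section Deviations from SAP shows that results are already known, so a re-analysis now should be reported as a documented deviation, not as if it had been pre-specified.

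The cost is revised wording and a rerun on existing data. The downside is that the paper would no longer offer a data-driven list of independent predictors. Multiplicity remains and is handled only by open reporting.

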## INTRODUCTION

Systemic Lupus Erythematosus (SLE) is a systemic autoimmune disease that may affect any organ. SLE is mostly associated with haematological abnormalities, rashes, arthritis/arthralgia, nephritis, and constitutional symptoms (1). Pulmonary diseases are common among SLE patients and affect up to 70% of the patients (2, 3), but the prevalence of PD among SLE patients are not investigated in a clinical study with a population-based design, to our knowledge. Prior studies have mostly investigated specific subgroups of PD and not PD in general. The PD commonly associated to SLE are airway disease, pleural disease, interstitial lung diseases (ILD), vasculitis, pulmonary haemorrhage, pulmonary hypertension, and the syndrome "Shrinking Lung Syndrome" (2-4).

Pulmonary Disease among SLE patients are important, as they are associated to an increased mortality (5) and decreased health-related quality of life (6). Unfortunately, there are a substantial difference between how patients report pulmonary symptoms and how physicians rate PD (7). It can be difficult to diagnose PD among SLE patients, for instance ILD is reported with a prevalence of 11-37% in clinical studies at tertiary centres (8-11) but only around 6% in register studies (12). To diagnose PD among SLE patients, healthcare providers need to have suspicion. We believe that a detail knowledge of how common different PD are among SLE patients will help guide physicians to be aware of which PD they should suspect and maybe subsequently investigate. Importantly, a study have shown, that immunosuppression can improve pulmonary function among SLE patients (13).

It is not always clear if pleura, pulmonary vasculature, and diaphragm are covered by the term "pulmonary disease". In the following we will refer to diseases of the pleura, airways, pulmonary vasculature, diaphragm, and lung parenchyma as pulmonary diseases (PD).

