## Deviations from SAP

In general:

Removed SLS from analysis, because only one was diagnosed with SLS why analyses were of limited value.

Some values have been changed in tables, to make them easier to understand.

Secondary objectives. Describe baseline characteristics has been removed, as it we did not find it was a relevant objective, but it is reported. Further, we have tried make the wording more concise to make them more readable.

Post hoc we developed Figure 2, Appendix 5, and fitted analyses. We included them, as they provided with important information.

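### Covariates for the multiple logistic models are chosen by univariate significance, with no limit tied to the number of cases, so adjusted odds ratios for small outcomes such as ILD would be biased away from 1

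*SAP*

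**What the plan says.** The regression section of the SAP sets out two steps. First: "Independent variables, as listed in Table 4 and appendix 3, will be analysed in univariate logistic regression", with an association flagged when its interval excludes 1 ("with 95% CIs excluding 1 considered indicative of potential significance"). Second: "In multiple logistic regression analyses we plan to investigate associations that were significant by univariate analyses". The section adds that only some variables should stay significant, which predicts the result and does not limit what may enter.

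The outcomes listed in the Results section are "presence of PD, airway disease, pleural disease, ILD, and SLS in a table, see table 4". One procedure serves all five, whatever their frequency. The section gives no maximum number of covariates, no minimum number of cases, no penalised or exact method, and no rule for choosing between overlapping versions of a measure.

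On frequency, the Introduction says "ILD is reported with a prevalence of 11-37% in clinical studies at tertiary centres" and puts register studies at around 6%. The SAP states no sample size. The section on deviations records: "Removed SLS from analysis, because only one was diagnosed with SLS".

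**The concern.** Maximum-likelihood odds ratios from logistic regression are biased away from 1 when there are few cases per estimated coefficient. This happens even if every covariate is a genuine predictor and no cell is empty. Screening on univariate significance adds a second upward bias, because variables enter partly when their estimate happens to be large in this sample.

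A long candidate list, a 5% entry threshold and a rare outcome expose the plan to both. Surviving variables would be described as independently associated with the condition. For ILD, the strength of those associations could be overstated. The SAP lists associations with PD subtypes as a secondary objective, so this matters for interpretation, although prevalence itself is not affected.

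**Working it through.** The SAP gives no sample size, case count or cases-per-coefficient figure, so there is no figure of its own to reproduce. N is an assumption throughout.

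**Candidate pool.** Table 4 has 25 variables and Appendix 3 has 42. SLEDAI 2K and SLICC DI appear in both, so 25 + 42 − 2 = 65 (64 if one of the two CTD-overlap rows is only a label). Pleuritis and pleural effusion are slashed out in the PD and pleural columns, leaving 65 − 2 = 63 there. At a nominal 5% threshold, chance alone would pass about 0.05 × 64 = 3.2 variables per outcome.

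**Cases.** Cases = N × prevalence, for N = 100 to 300:
- 6%: 6 to 18
- 11%: 11 to 33
- 37%: 37 to 111

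**Cases per coefficient if 10 coefficients were fitted.** Cases / 10 = 0.6-1.8 at 6%, 1.1-3.3 at 11% and 3.7-11.1 at 37%.

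**What the screen would deliver.** I simulated 64 candidates (correlation 0.5 within blocks), with entry at univariate p < 0.05, true odds ratio 1.5 and 250 runs per row. There were four true effects, except in the row marked with two. Odds ratios are for true predictors that passed the screen.

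| N | Prevalence | Median variables entered | Median cases per coefficient | Models at 2 or fewer | Models below 10 | ML OR | Firth OR |
|---|---|---|---|---|---|---|---|
| 150 | 6% | 4 | 2.25 | 48% | 97% | 2.29 | 1.95 |
| 150 | 11% | 5 | 3.00 | 30% | 89% | 1.83 | 1.69 |
| 200 | 6% | 4 | 2.60 | 39% | 95% | 1.89 | 1.73 |
| 200 | 11% | 6 | 3.40 | 15% | 92% | 1.66 | 1.58 |
| 200 | 11% (two true) | 5 | 4.80 | 6% | 85% | 1.66 | 1.59 |
| 300 | 11% | 8.5 | 3.81 | 5% | 91% | 1.53 | 1.49 |
| 200 | 20% | 7 | 5.29 | 1% | 84% | 1.53 | 1.48 |
| 200 | 37% | 10 | 7.60 | 0% | 73% | 1.50 | 1.46 |

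At 6-11% prevalence the medians lie between about 2 and 5 cases per coefficient. Two or fewer is frequent only at the smallest case counts.

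**Small-sample bias without screening.** With fixed sets of 6 to 10 covariates, N 150 to 300 and a true odds ratio of 2.0, the geometric-mean ML odds ratio was 2.15-2.60 at 6%, 2.05-2.29 at 11% and 2.01-2.23 at 37%. Firth fits stayed at 1.94-2.10.

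**Separating the two biases.** With fixed sets, Firth fitting brings the estimate back close to the truth. After screening at 6-11% it still gives 1.49-1.95 for a true 1.5. Penalisation therefore deals with sparse data but not with selection.

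**The case against.** The section is exploratory, the primary objective is prevalence, and the mock-up tables show univariate results only. The text does not literally say that all significant variables enter one model together. Participants have HRCT, lung function tests and a multidisciplinary discussion, so ILD may be found more often than in registers; at 37% with N = 200, the simulated screen gave no inflation and no model at two or fewer cases per coefficient. In fixed-set simulations (N = 200, true odds ratio 2.0), nominal 95% intervals kept 93-97% coverage, so the planned intervals would show much of the uncertainty. The figure of 3.2 chance entries is also on the high side: with 12 cases, binary covariates passed a Wald screen only 2-3% of the time, and many candidates are binary.

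Much of this stands, and it limits the size of the problem. It does not supply the missing limit. Univariate significance is the only entry criterion given, and a section that leaves model size open does not protect the rare outcomes. The coverage figures come from models without screening, so they do not answer the selection bias.

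Two stronger readings are tempting. A reader might infer that the ILD models will have only one or two cases per coefficient. That needs low prevalence, small N or many entered variables, none of which the SAP fixes. A reader might also take the single SLS case as evidence that ILD was sparse. The deviations section says nothing about ILD counts; it shows only that a sparse outcome was handled afterwards, with no rule in the SAP for it.

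**Conclusion.** The point holds in a limited form. The SAP selects covariates by univariate significance from about 65 candidates, with no limit tied to cases and no penalised fit. Ordinary logistic regression run that way overstates adjusted odds ratios for small outcomes. The likely size runs from slight (1.53 for a true 1.5 at N = 300 and 11%) to large (2.29 at N = 150 and 6%), and there is little or no bias for common outcomes. Every size rests on an assumed N, assumed true effects and assumed correlations; only the ILD prevalences and the candidate lists come from the SAP. The document does not show whether the multiple models were fitted as written. The point concerns a secondary objective and should be corrected.

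**What to change.** In the regression section, replace entry by univariate significance with a short, ranked list of covariates for each outcome, chosen on clinical grounds, and tie its length to the number of participants in the smaller outcome category. The exact ratio is the team's choice. As an illustration, the common but debatable convention of 10 cases per coefficient would allow 0 to 3 coefficients for ILD at 6-11% prevalence and 3 to 11 at 37% (N 100 to 300). Fit the models for ILD and any similarly sparse subtype with Firth penalised likelihood. Report the number of cases and coefficients beside each model.

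All parts are needed: a cap or Firth fitting alone leaves the bias from univariate screening in place.

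The cost is some SAP wording, modest changes to code, and fewer variables jointly adjusted for rare subtypes. The deviations section shows that results are already known, so a list drawn up now is not truly pre-specified. The refit should be logged as a deviation, with the reasons for each list stated.
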